## Abstract

**Background:**

Endometriosis is a chronic inflammatory condition affecting 6%-10% of women of reproductive age and is defined by the presence of endometrial-like tissue outside the uterus (lesions), commonly affecting the pelvis and ovaries. It is associated with debilitating pelvic pain, infertility, and fatigue and often has devastating effects on the quality of life (QoL). Although it is as common as back pain, it is poorly understood, and treatment and diagnosis are often delayed, leading to unnecessary suffering. Endometriosis has no cure. Surgery is one of several management options. Quantifying the probability of successful surgery is important for guiding clinical decisions and treatment strategies. Factors predicting success through pain reduction after endometriosis surgery have not yet been adequately identified.

**Objective:**

This study aims to determine which women with confirmed endometriosis benefit from surgical improvement in pain and QoL and whether these women could be identified from clinical symptoms measured before laparoscopy.

**Methods:**

First, we will carry out a systematic search and review and, if appropriate, meta-analysis of observational cohort and case-control studies reporting one or more risk factors for endometriosis and postsurgical treatment success. We will search PubMed, Embase, and Cochrane databases from inception without language restrictions and supplement the reference lists by manual searches. Second, we will develop separate clinical prediction models for women with confirmed and suspected diagnoses of endometriosis. A total of three suitable databases have been identified for development and external validation (the MEDAL [ISRCTN13028601] and LUNA [ISRCTN41196151] studies, and the BSGE database), and access has been guaranteed. The models will be developed using a linear regression approach that links candidate factors to outcomes. Third, we will hold 2 stakeholder co-design workshops involving eight clinicians and eight women with endometriosis separately and then bring all 16 participants together. Participants will discuss the implementation, delivery, usefulness, and sustainability of the prediction models. Clinicians will also focus on the ease of use and access to clinical prediction tools.

**Results:**

This project was funded in March 2018 and approved by the Institutional Research Ethics Board in December 2019. At the time of writing, this study was in the data analysis phase, and the results are expected to be available in April 2021.

**Conclusions:**

This study is the first to aim to predict who will benefit most from laparoscopic surgery through the reduction of pain or increased QoL. The models will provide clinicians with robustly developed and externally validated support tools, improving decision making in the diagnosis and treatment of women.

**International Registered Report Identifier (IRRID):**

DERR1-10.2196/20986

## Introduction

### Background on Endometriosis

Endometriosis is a chronic inflammatory condition affecting 6%-10% of women of reproductive age. It is defined by the presence of endometrial-like tissue outside the uterus (lesions), commonly affecting the pelvis and ovaries [1,2]. Although as common as back pain, it is poorly understood, and treatment and diagnosis are often delayed [2]. For example, in the United Kingdom, there is an average delay of 7-9 years in accessing treatment for endometriosis [3]. This is largely due to the lack of accurate, noninvasive diagnostic tests or biomarkers [4]. The diagnostic gold standard is pelvic laparoscopy under general anesthesia. Laparoscopy can be diagnostic, therapeutic, or both.

Diagnostic delays lead to unnecessary suffering, and endometriosis is associated with debilitating pelvic pain, infertility, and fatigue and can have devastating effects on the quality of life (QoL). Endometriosis has no cure, but there are a number of treatment options. These include drugs that suppress ovarian function (which can have adverse effects [5]) or surgery for the lesions (usually laparoscopically). Surgical removal is often considered the best option for symptomatic endometriosis [6], but it does not reduce pain in 20%-28% of patients who undergo surgery [7,8].

### Variable Response to Surgery

Quantifying the potential for improvement in a woman’s symptoms after surgery is important for guiding clinical decisions and treatment strategies. Secondary findings from observational, single-center studies indicate a graded response regarding pain reduction after endometriosis surgery, which is inversely related to disease severity [8-11]. One randomized controlled trial (RCT) found that pain symptoms improved after endometriosis surgery in significantly more patients with moderate and mild endometriosis (approximately 100% and 70%, respectively) than minimal disease (approximately 40%) [9]. In 2 other studies, women with deep endometriosis (DE) experienced more pain reduction after surgery than those with superficial endometriosis [10,11].

Although National Health Service (NHS) England recommends that women should undergo therapeutic laparoscopy for complicated DE in specialist endometriosis centers, we have no evidence-based information to recognize these women clinically. Nor are we able, at present, to recognize which women will respond to this treatment. As a result, therapeutic laparoscopy, a costly and limited resource with long waiting lists, is not necessarily carried out on those who will experience pain reduction.

Factors predicting pain reduction after endometriosis surgery have not yet been adequately identified, as they have never been studied as the primary research question. However, secondary outcomes from previous trials indicate that such factors can be identified [8,9,11]. Our aim is to address the existing gap by predicting success through pain reduction after endometriosis surgery.

## Methods

The CRESCENDO (Creating a Clinical Prediction Model to predict Surgical Success in Endometriosis) project will be undertaken using existing recommendations for prognostic research model development, validation [12-14], and reporting [15]. It will also involve a systematic review of clinical risk factors associated with endometriosis and postsurgery treatment success, which will adhere to the PRISMA (Preferred Reporting Items for Systematic Reviews and Meta-Analyses) guidelines [16]. The systematic review is registered in the International Prospective Register of Systematic Reviews (PROSPERO).

### Aim

To develop clinical prediction models for endometriosis to answer 2 fundamental questions regarding the surgical management of endometriosis:

Which women with confirmed endometriosis benefit from surgery and see improvement in pain and QoL? (Primary models)Could these women be identified based on clinical symptoms measured before laparoscopy? (Secondary models)

### Specific Objectives

To perform a systematic review of preoperative and intraoperative factors associated with postsurgical treatment success in endometriosis.To perform a systematic review of the clinical risk factors associated with endometriosis.To develop and validate clinical prediction models to predict changes in self-reported pain and QoL after surgery in women with a confirmed (primary models) or suspected (secondary models) diagnosis of endometriosis.To describe an implementation plan within the secondary care pathway for women with a confirmed or suspected diagnosis of endometriosis using co-design workshops.

### Systematic Review

We will carry out a systematic review and meta-analysis of observational cohort and case-control studies reporting 1 or more risk factors for endometriosis and predictors of postsurgical treatment success. We aim to determine the following:

Absolute risk of having endometriosis in the presence or absence of a given risk factor.Relative risk of having endometriosis in the presence or absence of a given risk factor.The population attributable fraction for endometriosis in relation to each risk factor.Pre- and intraoperative factors for postsurgical treatment success for endometriosis and the associated risks.

#### Literature Search

We will search PubMed, Embase, and Cochrane databases from inception without any language restrictions and supplement these with manual searches of reference lists of included primary studies and relevant review articles.

#### Study Selection, Data Extraction, and Quality Assessment

The first reviewers will independently screen the titles and abstracts to identify the eligible studies, followed by retrieval and assessment of full texts of potentially relevant articles. Any disagreement will be resolved following discussions with a different reviewer. We will extract data in duplicate using predesigned data extraction forms. We will assess the quality of methodology of the included studies using the Newcastle Ottawa Scale [17] or the Jadad score [18], depending on the study.

### Data Sets for Development of the Clinical Prediction Models

We have identified 3 suitable data sets that will be employed to develop and validate the clinical prediction models for women with confirmed and suspected diagnoses of endometriosis. We have guaranteed access to all three databases and data sharing agreements have been finalized *a priori*.

The British Society of Gynaecological Endoscopy (BSGE) maintains a national database that contains data of over 5000 women who had a confirmed diagnosis and underwent laparoscopic surgery for advanced endometriosis (stage 4). Records have been collected by clinicians at over 50 endometriosis centers in the United Kingdom since 2007 (data collection is ongoing). Endometriosis centers are commissioned by NHS England and accredited by the BSGE for complex multidisciplinary surgery required for the treatment of DE [19,20]. To maintain accreditation, the database serves as a mandatory record of DE cases and outcomes [21]. It includes data on patient characteristics, pain, and QoL before and 6, 12, and 24 months after surgery, along with intraoperative findings. It is the most comprehensive source of data on endometriosis surgery and QoL worldwide. Some of these data have recently been published [22].

The second data set comes from a clinical study of women with suspected endometriosis, specifically chronic pelvic pain. *MRI versus laparoscopy to diagnose the main causes of chronic pelvic pain in women: a test-accuracy study and economic evaluation* (MRI to establish diagnosis against laparoscopy [MEDAL]) [ISRCTN13028601], was a comparative test-accuracy study assessing whether magnetic resonance imaging (MRI) could replace or triage the use of laparoscopy in establishing a diagnosis among women presenting in secondary care with chronic pelvic pain. Data were collected on patient characteristics, pain, and QoL before and after diagnostic laparoscopy with or without surgery, along with intraoperative findings for over 300 women who underwent laparoscopic surgery for chronic pelvic pain at 26 UK hospitals. During surgery, over a third of the women were diagnosed with endometriosis [23].

The third data set included women with suspected endometriosis collected during an RCT. This study, *Laparoscopic Uterosacral Nerve Ablation (LUNA) for alleviating chronic pelvic pain* [ISRCTN41196151]*,* randomized 487 women with chronic pelvic pain from 18 UK hospitals to assess the effectiveness of laparoscopic uterine nerve ablation. No significant improvements were reported on the visual analog pain scales. The data collected were similar to MEDAL and included patient characteristics, pain, and QoL at multiple time points [24].

### Establishment of Data Sharing

The Queen Mary University of London pragmatic clinical trials unit (PCTU) will provide data management for secure data set transfer and storage in accordance with general data protection regulation and information governance principles. Data will be stored within a PCTU safe haven. No additional data collection will be needed. The MEDAL, LUNA, and BSGE data will be given to the PCTU in a pseudonymized form. The minimum data to be collected from the 3 data sets will be agreed upon by the study team, collaborators, and study steering committee. All recorded variables will be considered for collection.

### Data Preparation

Data will be supplied in the format convenient for the original researchers. This project will take responsibility for converting, cleaning, and formatting the data as required before analysis. MEDAL and LUNA are data sets from previous funded studies and have been quality checked, analyzed, and published in peer-reviewed journals. Therefore, we will not assess the quality of the data, and we expect a limited need to clean them. Analyses of the BSGE data set have recently been published [22]. However, we will receive the raw source data, which will require cleaning, data quality checks, and assessment of the availability of relevant data for inclusion in the analysis. The collection of BSGE data is ongoing, so matching results from previous publications will be limited.

The 3 data sets (BSGE, MEDAL, and LUNA) will be employed when creating the prediction models, either as *development* or *external validation* data sets. To enable external validation of the prediction models, the predictors in the development data set will be matched with the variables in the validation data set. Where a direct match is not available in the data, we will investigate whether a new variable can be created from other information, such as calculating BMI from weight and height or categorizing continuous variables into groups.

### Candidate Factors

A list of candidate factors will be finalized before model development begins. Different factors might be considered in the analysis of treatment success in women with confirmed and suspected endometriosis.

Candidate factors will be identified through expert clinical input as well as through a systematic review. We will use the single factors that were investigated in narrative systematic reviews [19,26] and factors that were used as a part of previous models. These are likely to overlap. We will confirm that any candidate factor is available in the data for the analysis.

### Sample Size Considerations

This study uses pre-existing data sets to develop and validate multivariable prediction models, and at the outset of this project, no formal guidance on the minimum sample size was available. The available records from all 3 data sets will be used. However, for confirmation and after completing the analysis, we will compare our results with recently published recommendations for sample size calculations in prognostic studies [27].

The BSGE data set contains records of approximately 5000 women, of which approximately one-third are complete. Data availability for analysis is likely to increase with the selection of candidate factors from the list of available variables.

The MEDAL data set contains records of over 300 women, with approximately 110 confirmed diagnoses of endometriosis. We assume no impact of the additional diagnostic test (MRI) performed in one arm of the study and therefore include the full study population in our analyses. The analysis of treatment success in women with suspected endometriosis will examine a reduced set of candidate factors that are available before diagnostic laparoscopy. We will ensure that the list of factors considered is appropriate for the available sample size.

The LUNA data set will serve as an external validation set for the model developed to predict treatment success in women with suspected endometriosis. We will include both the treatment and control arms of the trial, as no evidence of an effect of the LUNA intervention was found for any of the pain outcomes included. The LUNA data set contains records of over 590 women, with approximately 140 women with confirmed endometriosis.

### Model Development

A total of 2 groups of models will be developed, reflecting the 2 different populations of women we aim to study. The group of 5 primary models will predict treatment success in women with confirmed diagnoses according to the 5 outcomes described above. The second group will consist of 5 models that predict treatment success in women with suspected endometriosis. Overall, this will result in 10 distinct models.

For the primary models (for women with a confirmed diagnosis of endometriosis), we will use the BSGE data set; a randomly selected 10% of records will be removed for performance testing of the model. For the secondary models of women with suspected diagnoses, we will use the MEDAL data set. All models will be developed using a logistic regression approach, linking candidate factors to outcomes.

A backward selection process will be used to decide which of the candidate predictor variables should be included in the final models (with a cutoff value of *P*<.15 conservatively taken to warrant inclusion and prevent omission of important predictors); candidate factors will likely vary between the models.

Continuous variables will be kept as continuous in the models (and not dichotomized) to avoid loss of power. Nonlinear effects may be considered if allowed by the sample size. No imputation of missing data will be performed, but the missing data at random assumption will be investigated.

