### Model Performance and Internal Validation

After developing the models, we will assess how well they perform. Calibration will be assessed visually using scatter plots; the calibration slope will indicate whether predictions are systematically too high or low (calibration-in-the-large). The apparent performance of the final models will be evaluated in terms of discrimination using the C statistic.

As apparent performance is often optimistic (due to a model being developed and validated in the same data set), internal validation, which we refer to as model performance, will also be undertaken. For the primary models of treatment success in women with confirmed endometriosis, we will randomly divide the BSGE records into 2 data sets, development (90% of the data) and validation (10% of the data). The apparent performance of the models in the validation sample will be compared with their performance in the development data set. *Optimism* is the difference between the apparent value in the validation sample and the observed value in the development data set. This optimism estimate is then subtracted from the model’s apparent performance to obtain an optimism-adjusted estimate of each measure of performance for the model.

The sample size in the MEDAL data set is not sufficient to use the same approach for the secondary models of treatment success in women with suspected endometriosis. If deemed appropriate, we may implement a bootstrap resampling technique whereby the apparent performance of the developed model in bootstrap samples is compared with its performance in the model developed using the original data set.

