### Limitations

The use of pre-existing data collected as part of other projects means that we will be limited by the data as recorded and will have no input as to how and what information is collected. Nonetheless, we have been able to assess the extent of missing data and found it to be sufficiently low. Power considerations have been based on truly available data, and the large sample size, specifically in the BSGE data set, will allow us to investigate a wide range of prognostic factors.

A second limitation is the matching of variables in the development and external validation data sets. This challenge is common to many studies that use pre-existing external validation data sets. We have been comparing how data were collected in the data sets and found most variables to be compatible; however, not all factors that we may identify as prognostic will also be available in the validation data set, thereby limiting the list of prognostic factors that can be validated externally.

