### Main Outputs and Access

This study will provide robustly developed and externally validated prediction models for postsurgery treatment success in women with suspected or confirmed endometriosis. The models will be generalized to a large range of women with this condition. To our knowledge, this project will be the first to predict who will benefit most from laparoscopic surgery resulting in reduction of pain or increased QoL and is therefore much needed. The prediction models will provide clinicians with a supporting tool for improving decision making in the diagnosis and treatment of women, thereby reducing unnecessary costs and harms associated with laparoscopic surgery.

Upon completion of the entire study, the models will be put in the public domain and will potentially be available for immediate use. The plan is that patient characteristics and clinical data can be entered into the formula by the user to calculate an individualized prediction of improvement after surgery. Presentation, implementation, and uptake within secondary care will be refined and finalized after the co-design workshops and beyond the lifespan of this project. For example, access could be in the form of a website or phone app. Our work with patient groups in the co-design workshops will give us invaluable direction on how to best advertise and deploy the prediction models, ensuring the greatest possible gain for patients and clinicians.

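### No shrinkage is planned for coefficients chosen by backward selection, so the five MEDAL-based models are likely to give predictions that are too extreme

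*Protocol article*

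**What the plan says.** All references are to the protocol article.

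- **Model Development** sets one rule for every model: "A backward selection process will be used to decide which of the candidate predictor variables should be included in the final models". The cut-off is P<.15, "conservatively taken to warrant inclusion and prevent omission of important predictors". There are five outcomes in each of two populations: "Overall, this will result in 10 distinct models". Primary models are developed in a random 90% of BSGE and secondary models in MEDAL. Missing data are not imputed.
- **Candidate Factors** gives no number of candidates: "A list of candidate factors will be finalized before model development begins". **Sample Size Considerations** promises a reduced list for the secondary models that suits the sample size, also without a number.
- **Model Performance and Internal Validation** estimates optimism and subtracts it from apparent performance "to obtain an optimism-adjusted estimate of each measure of performance for the model". For MEDAL, a bootstrap may be used if judged appropriate. Table 1 lists bootstrap samples or another suitable method.
- **External Validation and Recalibration** allows, but does not require, recalibration or revision if performance in the new data is poor.
- **Main Outputs and Access** releases a formula "to calculate an individualized prediction of improvement after surgery".

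**The concern.** When the same data choose the factors and estimate their coefficients, the retained coefficients tend to be too large. Optimism then shows up in two places: in the reported performance and in each patient's predicted value. The plan corrects the first. Subtracting optimism from a C statistic leaves every coefficient, and so every prediction, unchanged.

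The product is an individual predicted change in pain or QoL for use in deciding about surgery. With a calibration slope of 0.70, a woman predicted to differ from the average change by 2 VAS points would be expected to differ by 2 × 0.70 = 1.4. Women predicted to do well look better than they will be, and women predicted to do poorly look worse.

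A second, smaller issue is interpretation. The Limitations section remarks that "not all factors that we may identify as prognostic will also be available in the validation data set". If factors come to be called prognostic because they survived P<.15, the evidence behind that label is thin.

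**Working it through.** The article gives no figure for overfitting or shrinkage, so there is nothing to reproduce.

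**Inputs from the article.** The cut-off is P<.15 (taken as two-sided). MEDAL has over 300 women, so n = 300; with no imputation the usable number may be lower, by an amount not stated. BSGE has about 5000 records, about one third complete, with 90% used for development: 5000 × 1/3 × 0.9 = 1500. If almost all records proved usable, the upper bound is 5000 × 0.9 = 4500.

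**Assumed inputs.** Number of candidates k = 10 (3 truly predictive) or 20 (4 truly predictive); correlation between candidates 0.2; true R² = 0.05, 0.10 or 0.20.

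**Step 1: noise retention when nothing predicts.** With independent candidates, P(at least one kept) ≈ 1 − 0.85^k.

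| k | 1 − 0.85^k |
|---|---|
| 4 | 47.8% |
| 5 | 55.6% |
| 10 | 80.3% |
| 15 | 91.3% |
| 20 | 96.1% |

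The figure passes one half at k = 5. Simulated backward elimination in linear regression agrees: 77–81% at k = 10 and 95–97% at k = 20, with little dependence on n. With real predictors present at the assumed R² values and n = 300 or 1500, 65–76% (k = 10) and 90–93% (k = 20) of models still keep at least one noise factor.

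**Step 2: calibration slope in new patients from the same population.** Backward elimination at P<.15, linear regression, coefficients left unshrunk, mean slope:

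| True R² | n = 300, k = 10 | n = 300, k = 20 | n = 1500, k = 10 | n = 1500, k = 20 |
|---|---|---|---|---|
| 0.05 | 0.69 | 0.53 | 0.95 | 0.87 |
| 0.10 | 0.85 | 0.70 | 0.96 | 0.93 |
| 0.20 | 0.94 | 0.87 | 0.98 | 0.97 |

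Repeat runs move single entries by about 0.02, which is why the upper end at n = 300 and R² = 0.05 is quoted as 0.71 and the upper end at n = 1500 as 0.99. At n = 4500 the slopes are 0.96–1.00.

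**Step 3: model type.** The Abstract names linear regression and Model Development names logistic regression. A logistic version (coefficient 0.3 for each true predictor) gives 0.75 (k = 10) and 0.64 (k = 20) at n = 300, and 0.94 and 0.92 at n = 1500. The pattern is the same.

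**Step 4: is the cut-off the cause?** At n = 300, k = 20, R² = 0.10 the slope is 0.76 with P<.05, 0.70 with P<.15 and 0.62 with all candidates kept. The cut-off contributes little. The main causes are few women per candidate and no shrinkage.

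**The case against.** Several stronger readings are tempting, and the article does not support them.

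- *A reader might infer that the coefficients can never be altered.* External Validation and Recalibration allows recalibration or revision, and release follows completion of the study. This stands. But the step is optional and has no trigger. Carried out in LUNA, it would also mix overfitting with differences between settings. The plan moreover reads the calibration slope as a check on average over- or under-prediction, which is what the intercept shows; an over-extreme model could pass that check.
- *A reader might infer that all ten formulas are affected alike.* They are not: the BSGE models are large enough for the effect to be small.
- *A reader might blame P<.15, or call the word conservative a mistake.* Step 4 shows that the cut-off is not the main cause. The sentence itself explains the word as protection against omitting predictors, and a liberal cut-off serves that aim.
- *A reader might infer that the rule cannot tell true factors from noise.* It can when signal is strong. With R² = 0.20 shared equally by three independent predictors at n = 300, each has noncentrality 300 × 0.0667/0.8 = 25 (z about 5) and is almost always kept, against about 15% for a noise factor. Candidates also come from expert input and reviews, so a complete absence of predictors is unlikely.
- *A reader might take the Limitations remark as a claim that P<.15 proves prognosis.* It concerns the matching of variables between data sets.

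Finally, a condensed article may leave shrinkage to the analysis plan. That has some force. However, the article does state the selection rule, the cut-off and what the optimism correction is applied to. Followed as written, it yields unshrunk coefficients unless an optional step is taken.

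**Conclusion.** The point holds for the five secondary models. In about 300 MEDAL women, the stated procedure would be expected to give slopes of about 0.87–0.94, 0.70–0.85 or 0.53–0.71 at a true R² of 0.20, 0.10 or 0.05, and lower still if many records are incomplete. For the five primary models, at about 0.87–0.99 with 1500 women and closer to 1 with more, it is minor unless signal is very weak and the candidate list long.

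The slopes rest on assumed values of k, R² and correlation. A short list, or strong predictors, would make the problem mild even in MEDAL. The retention result needs at least five candidates and describes the case in which none predicts. It supports caution in calling retained factors prognostic, not a claim that the selection is uninformative. This is an improvement worth making, not a flaw that invalidates the project.

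**What to change.** P<.15 and its wording can stay. At least for the MEDAL models:

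1. Make the bootstrap a commitment and repeat the full backward selection in every bootstrap sample.
2. Multiply the coefficients of each final model by the mean bootstrap calibration slope and re-estimate the intercept, before validation in LUNA and before release. Penalised regression (lasso or elastic net) is an alternative that selects and shrinks in one step.
3. Report each factor's bootstrap inclusion frequency, and describe factors as retained in the model rather than as prognostic on P<.15 alone.

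This uses data already held. It costs a few sentences and a little more analysis. Predictions become slightly less spread out, and some retained factors will be shown to be unstable.
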